## Abstract

**Background:**

Dementia has a high burden for patients, informal caregivers and society. Given changes in care systems, more persons with dementia will live longer at home. However, living at home (with dementia) with a good quality of life is not easy to achieve. Dementia is often accompanied by neuropsychiatric symptoms like apathy, agitation, depression, and anxiety, which have a negative impact on quality of life. Whereas cognitive deterioration can hardly be influenced, it is possible to reduce neuropsychiatric symptoms. As autobiographical memories remain intact for a relatively long time in dementia, reminiscence interventions can promote feelings of pleasure and trust. The Online Life Story Book (OLSB) allows to digitally share memories (stories, pictures, video or audio fragments). The main objective is to study the effects of the OLSB on neuropsychiatric symptoms. The study has four secondary objectives: 1) to study the effectiveness of the intervention on the burden and quality of life of the primary informal caregiver; 2) to provide a preliminary health-economic evaluation; 3) to study the (time to) nursing home admittance as a longer term effect; 4) to provide a process evaluation.

**Methods and design:**

A randomized controlled trial with individual randomization to one of two conditions is conducted: 1) intervention “Online Life Story Book”; 2) control condition (care as usual). Participants are persons with early dementia and their primary caregivers. In the intervention OLSB, a trained volunteer guides the participants through the process of putting together a timeline of their lives during 5 meetings within a period of 8-10 weeks. To assess the effects of the intervention on the primary outcome, neuropsychiatric symptoms, the Neuropsychiatric Inventory (NPI) will be assessed at three time points: before the intervention (baseline, T0), 3 months (T1) and 6 months (T2) post baseline.

**Discussion:**

When proven effective, the Online Life Story Book can be a valuable addition to the existing provision of care for persons with dementia and their informal caregivers.

**Trial registration:**

This study has been approved by the Twente Medical Ethics Committee under the file number p16-04 (Dutch Trial Register: NTR5939, date of registration: 14 March 2016).

## Background

At present, the number of people living with dementia worldwide is estimated at 47.5 million. This number will increase to 75.6 million in the coming 15 years. Dementia is among the top-5 with the highest burden of disease for persons over 65 years and it belongs to the diseases with the highest burden for informal caregivers. This burden includes physical, emotional and economic pressure. With costs over 604 billion US dollars it is one of the most costly diseases as well [1].

In the Netherlands, about two thirds of persons with dementia is estimated to live at home, but given the impact of the ageing population this number will increase. This is also in line with the preferences of persons with dementia and their informal caregivers [2]. However, living at home with a good quality of life is not easy to achieve.

Dementia is often accompanied by the presence of neuropsychiatric symptoms (NPS), like apathy, agitation, depression, anxiety, and delusions. A systematic review of studies on the course of NPS in community-dwelling patients with dementia found a cumulative prevalence of any neuropsychiatric symptom between 49% and 95% [3]. Delusions, agitation, aberrant motor behavior and apathy are the most common NPS [3]. Neuropsychiatric symptoms not only affect the quality of life of the patient [4], but also result in a higher burden of informal caregivers and a lower quality of their lives [4–6]. NPS are among the most important reasons for nursing home admittance, as they often make the care at home too burdensome [7]. Whereas it is still not possible to treat dementia, dementia care focuses mainly on maintaining quality of life and preventing psychosocial problems [8].

There is evidence that neuropsychiatric symptoms can be prevented or diminished by behavioral interventions [9]. However, it is important that such interventions fit the experiences and life world of persons with dementia well so that they can contribute to the needs of the persons with dementia and their informal caregivers [10].

The Online Life Story Book (OLSB) is such an intervention that nicely ties in with changes in care systems that promote persons with dementia to be living longer at home instead of moving to a nursing home. The Online Life Story Book has a different approach than most existing applications as it focuses on the unique life story rather than on specific complaints and symptoms. The OLSB builds on research on reminiscence [11]. Research has shown that remembering and reliving precious personal memories can create feelings of pleasure, familiarity, and assurance. Hence, reminiscence interventions are part of the Dutch standard for dementia care [12]. Personal memories belong to the autobiographical memory system, a part of memory that remains intact in dementia for a relatively long time [13, 14]. Most persons with early dementia are able to retrieve personal memories and share them. And even in later phases of the disease, they can still relive the positive feelings associated with precious memories. When the disease progresses and memory further deteriorates, it becomes more and more important to offer multisensory cues for memories in a structured way that fits the unique life story of the person with dementia. Under these conditions, reminiscence interventions can contribute to the psychosocial functioning of persons with dementia [15].

Several systematic reviews have shown that reminiscence activities can contribute to the mental health and quality of life of persons with dementia [15–18]. The use of life story books with personal memories that were constructed together with the person with dementia is especially promising [18]. Besides the recollection of personal memories, the collection of a person’s life story in a book adds to this [19].

The current study aims to test the effects of the OLSB in comparison to care as usual. The current study adds in three ways to the existing knowledge about the use of life story books for persons with dementia: 1) by assessing effects on NPS in the home situation; 2) by using technology; 3) and by employing volunteers in the intervention.

### Assessing effects in the home situation

The current project is one of the first to use life story books in the home situation. Informal caregivers are in need of meaningful activities that allow them to step out of the caring role [20]. Mutual reminiscence is such an activity that can also give rise to further activities in everyday life such as listening to music together, or cooking an all-time favorite recipe. This helps to decrease NPS and promote quality of life of the person with dementia. Moreover, it aids in reestablishing a more personal relation with the person with dementia. It diminishes the burden of the informal caregiver and improves his or her quality of life.

### Using technology

The current project is innovative as it assesses the use of life story books that have been created with modern information and communication technology. Technology plays an increasing role in dementia care, whether in domotica, remote care, or mobile apps [21]. This also fits the increasing competences of older persons to use computers and the internet [22]. About 85% of the Dutch persons between 65 and 75 years already use the computer and the internet at least once a week [23]. The use of technology has three major advantages [24]. First, technology makes it easier to document and retrieve personal memories that match the idiosyncrasies of individual life stories. Second, technology provides multimedia for the storage and retrieval of memories. Sound, music, photos, and movies can be easily added, besides anecdotes and verbal cues. Indirectly smell, taste, and touch can be used, for example by cooking a favorite recipe or doing preferred activities together. This becomes even more important when it becomes more difficult for the person with dementia to retrieve memories through verbal stimuli. Third, technology makes it possible to use the life story book in an interactive way. Informal caregivers and family members and friends can add new memories or remarks on memories that were especially vivid to them. Hereby, it is possible to update and adjust the life story book even when the dementia progresses. A recent review shows that the use of technology for reminiscence intervention is promising, but that there is still a lack of systematic studies in this field [24].

### Employing volunteers

Given the changes in healthcare systems around the world in which more people will live longer at home instead of moving to a nursing home, not only informal caregivers but also volunteers play an increasing role and are expected to participate more and more to provide care in everyday life. For care institutes the delivery of the intervention will become more efficient than care provided by a professional [25]. For older adults, an intervention delivered by a volunteer will be less stigmatizing than care by a healthcare professional such as a psychologist, in particular while volunteers provide a new contact with society [26]. It is well-known that volunteering supports both the volunteer’s mental health and well-being and that of the people they serve [27]. Volunteers like to contribute to projects with a concrete goal, limited time investment, and possibilities for training [28]. The current project suits both altruistic and self-oriented motivations of volunteers as it offers the possibility to create something of personal value to the person with dementia and the informal caregiver, whereas it also allows them to learn new competences in the training [29, 30]. The volunteer provides the necessary structure and the needed social and technological competences that serve to ease the task for the informal caregiver. As the intervention is based on reminiscence as a naturally occurring process in later life, volunteers can easily stimulate conversations about personal memories with the help of a well-defined protocol [11].

In summary, the primary objective of the study is to assess the effectiveness of the intervention “Online Life Story Book” on neuropsychiatric symptoms of persons with early dementia, in comparison to care as usual. The study has four secondary objectives: 1) to study the effectiveness of the intervention OLSB on the burden and quality of life of the primary informal caregiver; 2) to provide a preliminary health-economic evaluation by analysing the effects on the quality of life and care consumption of the person with early dementia; 3) to study the (time to) nursing home admittance as a longer term effect; 4) to provide a process evaluation.

## Methods and design

### Study design

A randomized controlled trial with individual randomization to one of two conditions is conducted:The intervention condition: participants in the intervention “Online Life Story Book”The control condition: participants receive care as usual.

The participant flow can be found in Fig. 1. The study takes 6 months for each individual participant with a baseline measurement (T0) as well as measurements after three (T1) and 6 months (T2). The intervention, creating an OLSB, takes about 8–10 weeks. The study takes place at the home of the person with early dementia who participates in the study. A trained volunteer will support the construction of the OLSB. Trained student assistants and the primary researcher will carry out the measurements.

**Fig. 1 Fig1:**
[figure not shown]
Study flowchart

This study has been approved by the Twente Medical Ethics Committee under the file number p16-04 (Dutch Trial Register: NTR5939). Participation is voluntary and all respondents will provide written informed consent before inclusion.

### Participants

#### Recruitment

We include persons with early dementia who are living at home and are being cared for by informal caregivers. In Enschede and Haaksbergen (two medium size cities in the Eastern part of the Netherlands) alone, there are 2500 persons with dementia. Livio, a large organization providing elderly care in this region, is in contact with about 575 of them through home care and living facilities for independently living older persons. Stichting Informele Zorg Twente, a local welfare organization, is in contact with about 650 informal caregivers. If the inclusion of 106 participants poses problems, participants can be recruited through other large care groups of the University Network for Elderly Care (UNO-UMCG), a network consisting of 16 large care organizations in the Northern and Eastern part of the Netherlands. We will recruit participants via so called Alzheimer Café’s, meeting centers for persons with early dementia, general practitioners and advertisements in newsletters for elderly people in the region.

#### Assessment of inclusion and exclusion

##### Inclusion and exclusion criteria

In order to be eligible to participate in this study, a subject must meet the following criteria:(Very) mild dementia;Living at home and receiving informal care;Being mentally capable to provide informed consent.

A potential subject who meets the following criterion will be excluded from participation in this study:Past psychotrauma.

##### Inclusion criteria

The main inclusion criterion is (very) mild dementia (Clinical Dementia Rating 0.5 or 1). This will be assessed with the Clinical Dementia Rating Scale [31]. This is a semi-structured interview that is carried out partly with the person with dementia and partly with the informal caregiver. The part for the person with dementia focuses on memory (10 items), orientation (8), and judgment/problem solving (9). The part for the caregiver asks for memory (15 items), orientation (8), judgment/problem solving (6), community affairs (10), home & hobbies (5), and personal care (4). The answers are used to compute a score ranging from 0 = none, 0.5 = very mild, 1 = mild, 2 = moderate to 3 = severe. Participants are included when they score 0.5 or 1. The other inclusion criteria are checked by the researcher during the baseline measurement.

##### Exclusion criterion

Psychotrauma is studied with the module posttraumatic stress disorder (PTSD) of the Mini International Neuropsychiatric Interview (MINI) that enables classification in DSM-categories [32]. The module consists of 14 dichotomous questions and 3 open questions that address current and lifetime PTSD. Participants are excluded when they report current or lifetime PTSD.

#### Sample size calculation

Based on systematic reviews [15, 17, 18], a small significant effect is expected for the primary outcome at follow-up. Hence, 74 participants are needed (GPower: f = 0.15; alpha = .05; power = .80; repeated measures anova with 2 groups and 3 measurement points; *r* = .50 between measurements). Given the vulnerability of the participants and a high mortality rate, we expect a drop-out of 30% [15, 17, 18]. Hence, 106 participants need to be included, 53 per condition.

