#### Effects

To analyze the effects on the primary outcome (total neuropsychiatric symptoms), repeated measures MANOVA will be used to assess the group differences across time. The condition (intervention vs. control) is the independent variable and the outcome measures across the three measurements are the repeated dependent variables. Simple contrasts will be used post-hoc to compare the post-intervention and follow-up measures with the pre-intervention measures. Effect sizes at post-intervention and follow-up will be calculated as Cohen’s d. Effect sizes between .56 and 1.2 are interpreted as large, between .33 and .55 as moderate, and below .33 as small [53].

We will also tentatively study the effects of the intervention on the four clusters of neuropsychiatric symptoms (hyperactivity, psychosis, affective symptoms, and apathy). As these measures are often not normally distributed, we will use a dichotomized outcome (clinically relevant symptoms or not, based on a FxS score of 4 and higher) [43]. We will carry out four logistic regression analyses with condition (intervention versus control) and presence of clinically relevant symptoms within the respective clusters at baseline as independent variables and presence of clinically relevant symptoms at follow-up as dependent variable. The odds-ratios will be used to provide estimates of the effect sizes in terms of Cohen’s d.

For the secondary outcome measures, three repeated measures MANOVA’s will be conducted, similar to the analysis for the primary outcome. The effect sizes will be given in Cohen’s d.

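### The sample size claims 80% power for a small effect, but f = 0.15 in the routine that yields 74 means d of about 0.64 or more, large on the protocol's own scale; power for a small effect is below 30% with 74 completers and r = .50

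*Protocol article*

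**What the plan says.** Protocol article, Sample size calculation: "a small significant effect is expected for the primary outcome at follow-up. Hence, 74 participants are needed (GPower: f = 0.15". The other inputs are alpha .05, power .80, a correlation of .50 between measurements, and a "repeated measures anova with 2 groups and 3 measurement points". Allowing for 30% drop-out, the section concludes: "Hence, 106 participants need to be included, 53 per condition". The GPower routine is not named, and f is not translated into a difference between the arms.

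Protocol article, Effects: the primary outcome (NPI total) is analysed with a repeated measures MANOVA of group differences over T0, T1 and T2. Cohen's d is reported at post-intervention and at follow-up and is graded as follows: "Effect sizes between .56 and 1.2 are interpreted as large, between .33 and .55 as moderate, and below .33 as small".

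Protocol article, Randomization: allocation takes place after the baseline measurement.

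**The concern.** The label f = 0.15 has no single meaning in repeated measures designs. In a test of the average difference between two groups, f is half of d, so 0.15 would mean d = 0.30, which is small. In a test of the group-by-time interaction, f is the standard deviation of the interaction means divided by the outcome standard deviation, and the same 0.15 stands for a much larger difference between the arms at follow-up. If 74 comes from the second kind of test, the stated 80% power belongs to a large effect. This paragraph is the only justification for the sample size. A reader who trusts it would take a non-significant primary result as evidence against the small benefit that the authors expect, although the trial would miss such a benefit most of the time.

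**Working it through.** **Inputs.** From Sample size calculation: f = 0.15, alpha = .05, power = .80, k = 2 groups, m = 3 measurements, r = .50, N = 74 evaluable, 106 enrolled. From Effects: the cut-offs for d. From Randomization: baseline precedes allocation, so the expected difference at T0 is zero. Sphericity is assumed (equal correlations of .50).

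**Step 1: reproduce 74.** For the interaction, the noncentrality is λ = f²·N·m/(1 − r), with df1 = (k − 1)(m − 1) = 2 and df2 = (N − k)(m − 1).

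- N = 74: λ = 0.0225 × 74 × 3 / 0.5 = 9.99, df 2 and 144, power 0.806.
- N = 73 also just passes (0.8006); 74 is the next even number.
- Drop-out: 74 / 0.70 = 105.7, rounded up to 106.

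Both stated figures therefore reproduce. With the same inputs, other routines give:

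| Routine | N for 80% power | Power at N = 74 |
|---|---|---|
| Group-by-time interaction | 74 | 81% |
| Time factor alone (same λ and df when k = 2) | 74 | 81% |
| Interaction, multivariate (MANOVA) form | 76 | 80% |
| Between-group factor, λ = f²·N·m/(1 + (m − 1)r) | 236 | 34% |
| Interaction, SPSS-type definition of f | 218 | 34% |
| Interaction, Cohen-type definition of f | 216 | 35% |

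Only tests involving time, with λ = f²·N·m/(1 − r), come near 74. The interaction is also the test that Effects plans.

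**Step 2: convert f to d.** Let δ₀, δ₁, δ₂ be the differences between the arms at T0, T1 and T2 in standard deviation units. With equal groups, f² = (1/4) × the variance of (δ₀, δ₁, δ₂), using divisor 3.

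- Difference at T1 and T2, (0, d, d): variance 2d²/9, so f = d/√18 = 0.2357d. At f = 0.15, d = 0.64.
- Linear build-up, (0, d/2, d): variance d²/6, so f = d/√24 = 0.2041d. At f = 0.15, d = 0.73.
- Difference at T2 only, (0, 0, d): the same f as the first pattern, d = 0.64.

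With zero difference at T0 and later differences between 0 and d, the variance cannot exceed 2d²/9. So 0.64 is the smallest d that f = 0.15 can represent, and it lies in the large band (.56 to 1.2).

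**Step 3: power for a small effect at N = 74, r = .50.** Here N·m/(1 − r) = 444, so λ = 444·d²/18 or 444·d²/24.

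| d | λ, (0, d, d) | Power | λ, linear | Power |
|---|---|---|---|---|
| 0.20 | 0.99 | 13% | 0.74 | 11% |
| 0.30 | 2.22 | 24% | 1.67 | 19% |
| 0.33 | 2.69 | 29% | 2.02 | 22% |

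A simulation of the interaction F test for (0, d, d), with 37 per arm and 20,000 runs, gave 13.1%, 24.1% and 28.8% for these three values and 80.6% at d = 0.636. The multivariate form gives 28% at d = 0.33. The planned simple contrast of change from baseline gives 29%.

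**Step 4: what 80% power for a small effect would take.** For (0, d, d), d = 0.33 needs 268 evaluable participants (383 enrolled at 30% drop-out), and d = 0.30 needs 324 (463 enrolled). These figures show the size of the gap; they are not a request to enlarge the trial.

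**The case against.** The arithmetic in the paragraph is right: 74 and 106 follow from the inputs. The planning section works in f, whereas the cut-offs in Effects apply to d and grade observed results, so the contradiction appears only after a conversion that assumes a pattern of means. The routine is inferred, not stated. It can also be said that 74 completers is a pessimistic basis, because Missing values plans multiple imputation so that all randomized participants are analysed, and that the correlation may exceed .50.

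Some of this stands. The fault is the effect attached to the numbers, not the numbers themselves. The figure of below 30% is tied to 74 completers and r = .50. With all 106 fully observed, power at d = 0.33 is 40%, and 80% is reached between d = 0.50 (76%) and d = 0.55 (84%) for a difference at T1 and T2, which is moderate. That is an upper limit, since imputation cannot restore everything lost to 30% drop-out. With 74 completers, power at d = 0.33 would be 45% at r = .70 and 63% at r = .80, values that the protocol does not assume. A baseline-adjusted analysis of one follow-up would give 37%.

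None of these reaches 80% for a small effect. The conversion needs only a zero expected difference at baseline, which randomization supplies, and later differences no larger than d. How 0.15 was chosen is not documented. Halving a d of 0.30, the between-group conversion, would produce it, but that is conjecture and nothing here depends on it.

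**Conclusion.** The concern holds. As written, the protocol claims 80% power for a small effect at follow-up, and the design does not have it. The calculation that gives 74 has 80% power for d of about 0.64 (difference at T1 and T2) to 0.73 at T2 (linear build-up), which the protocol itself calls large. For d = 0.33 power is 29% or 22% respectively, so a true effect at the top of the small range would be missed more than 70% of the time. This rests on the stated alpha, r = .50 and 74 completers, on equal expected means at baseline, and on the routine being one that tests time or group-by-time. That last point is inferred, but none of the between-group, SPSS-type or Cohen-type alternatives gives fewer than 216. The exact percentages move with the correlation and with the number observed; the failure to reach 80% for a small effect does not change in any of the cases checked.

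**What to change.** Reword the Sample size calculation:

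- Name the test (group-by-time interaction, if that was the routine used) and state that 74 completers give 80% power for a difference between arms of about d = 0.64 at T1 and T2, or about d = 0.73 at T2 if the effect grows linearly.
- Say that this is a large effect on the scale in Effects, and that power at d = 0.33 is below 30% with 74 completers and r = .50. Remove the description of the target effect as small.
- Add that the result will be read from the confidence interval for the difference, and that a non-significant test does not exclude a small or moderate effect.

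If the primary analysis were changed to a baseline-adjusted comparison at T2, its detectable difference should be quoted instead. With 37 per arm and r = .50, the standardised difference becomes d/√(1 − 0.25), and d = 0.57 gives 0.57/0.866 = 0.66, with power of about 80%.

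The cost is a rewritten paragraph and a less favourable statement of power. Enrolment, randomization and data collection are unaffected.

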#### Missing values

Multiple imputation (five data sets) will be used to replace missing values and carry out the analyses on the pooled data set. Hence, all participants who were randomized can be included in the statistical analyses. The results from this imputed intention-to-treat sample will be compared to the results of the observed data only.

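### Five imputations are too few for the 30% drop-out expected: the primary p-value depends on the random seed, and about 3 to 5 points of power are lost needlessly

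*Protocol article*

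**What the plan says.** In the Sample size calculation section, "74 participants are needed" for a repeated measures ANOVA with f = 0.15 and a correlation of .50. The authors then write "we expect a drop-out of 30" per cent, and conclude that "106 participants need to be included, 53 per condition".

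The Missing values section fixes the handling of those losses: "Multiple imputation (five data sets) will be used to replace missing values and carry out the analyses on the pooled data set". The stated purpose is that "all participants who were randomized can be included in the statistical analyses". An analysis of the observed data serves only as a comparison, so the imputed intention-to-treat result is in effect the main one.

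The Effects section applies a repeated measures MANOVA to the total Neuropsychiatric Inventory (NPI) score at T0, T1 and T2, with simple contrasts against baseline. Nothing in the article links the number of imputations to the expected drop-out or foresees a larger number.

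**The concern.** With five imputations, the variance between imputed data sets is estimated on only 4 degrees of freedom. The pooled estimate also still carries visible simulation noise. Both problems grow with the share of missing information, and a 30% loss makes that share substantial. They remain under textbook pooling, so this is a separate question from how the data sets are combined.

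Two things are at stake. First, another seed on the same data can move the primary result across .05. The planned comparison of imputed and observed-data results carries the same noise, so part of any gap between them may be random. Second, some power is given up that could be kept without recruiting anyone. The protocol plans 80% power for an effect it calls small, so a borderline result is a realistic prospect.

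**Working it through.** **Inputs from the protocol.** f = 0.15, alpha .05, power .80, 2 groups, 3 measurements, r = .50, N = 74, 30% drop-out, 106 randomised 1:1 (Sample size calculation); m = 5 imputations (Missing values).

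**Assumptions not in the protocol.** Data missing at random, normal outcome, no auxiliary variables, correct Rubin-type pooling, and drop-out either 15% by T1 and 30% by T2, or all 30% by T1.

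**1. The plan's own figures.** For the group-by-time interaction, the noncentrality is f² × N × 3/(1 − r) = 0.0225 × 74 × 3/0.5 = 9.99, on 2 and 2 × 72 = 144 df. Power is .806. Then 74/0.70 = 105.7, so 106. Both figures reproduce, and the sample size is not at fault.

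**2. Fraction of missing information (FMI).** Simulating 106 participants with these inputs and Bayesian normal imputation gives an FMI of 0.24 to 0.26 for the T2 contrast. The range 0.20 to 0.35 is used below.

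**3. Noise from finite m.** The variance of the pooled estimate is multiplied by 1 + FMI/m. The SD of the estimate between reruns, in units of its standard error with unlimited imputations, is √(FMI/m):
- m = 5: √(0.20/5) = 0.20 to √(0.30/5) = 0.245.
- m = 50: √(0.20/50) = 0.063 to √(0.30/50) = 0.077.

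**4. Degrees of freedom (Barnard-Rubin, complete-data df 104).** With λ = (1 + 1/m) × FMI/(1 + FMI/m), ν₁ = (m − 1)/λ² and ν₂ = (105/107) × 104 × (1 − λ), the pooled df are 1/(1/ν₁ + 1/ν₂). For FMI 0.25 and m = 5: λ = 1.2 × 0.25/1.05 = 0.286, ν₁ = 49.0, ν₂ = 72.9, df = 29.3. With m = 50 the df are 69.2.

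**5. Power for a single contrast.** Set the effect so that unlimited imputations give 80%. At FMI 0.25 this is a noncentrality of 2.837. With m = 5 it becomes 2.837/√1.05 = 2.769 against a critical t of 2.044, giving 76.3%. With m = 50 it is 2.830 against 1.995, giving 79.7%.

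| FMI | df, m = 5 | df, m = 50 | Power, m = 5 | Power, m = 50 | Shortfall from 80%, m = 5 |
|---|---|---|---|---|---|
| 0.20 | 38.4 | 76.1 | 77.3% | 79.8% | 2.7 |
| 0.25 | 29.3 | 69.2 | 76.3% | 79.7% | 3.7 |
| 0.30 | 22.9 | 62.6 | 75.2% | 79.6% | 4.8 |
| 0.35 | 18.3 | 56.4 | 74.0% | 79.5% | 6.0 |

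**6. Power by simulation.** There were 3000 trials per row, with N = 106 and the effect scaled to f = 0.15. Shape is the relative group difference at T0, T1 and T2. The 2-df test is the pooled test of the T1 and T2 changes.

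| Shape | Missing T1/T2 | T2 contrast, m = 5 / 50 | 2-df test, m = 5 / 50 |
|---|---|---|---|
| 0, 1, 1 | 15%/30% | 75.8 / 79.5 | 81.8 / 85.7 |
| 0, 1, 1 | 30%/30% | 74.4 / 78.5 | 77.1 / 82.9 |
| 0, 0.5, 1 | 15%/30% | 87.0 / 89.7 | 80.6 / 84.7 |
| 0, 0.5, 1 | 30%/30% | 84.7 / 88.1 | 76.1 / 81.6 |
| 0, 0, 1 | 15%/30% | 74.6 / 79.1 | 79.4 / 83.6 |
| 0, 0, 1 | 30%/30% | 73.8 / 78.0 | 75.3 / 81.5 |

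The loss is about 3 to 5 points for the T2 contrast and 4 to 6 for the 2-df test.

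**7. Seed dependence.** When T1 and T2 differ equally by d, f = (d/2) × √(2/9). So d = 0.64 corresponds to the planned f = 0.15, and d = 0.5 to f = 0.12.
- 2-df test, d from 0.5 to 0.64 (150 data sets per scenario, 600 imputations each, resampled): two runs disagree on p < .05 in 7% to 15% of trials with m = 5, against 1% to 3.5% with m = 50. A further simulation gave 10% to 13% against 3% to 4%.
- T2 contrast at f = 0.15: two seeds with m = 5 disagree in about 8% to 12% of trials.
- 2-df test, many-imputation p between .02 and .10: two runs disagree in 36% to 40% of cases with m = 5, against 9% to 16% with m = 50.
- T2 contrast, p between .02 and .10 with 100 imputations: the p-value over 20 seeds with m = 5 has an SD of about .04 and a typical range of about .015 to .17.

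**The case against.** The strongest reply is that nothing here invalidates the trial. In simulations under no effect, five imputations rejected in 4.2% to 4.7% of trials, so type I error is held. Relative efficiency at FMI 0.30 is already 1/(1 + 0.30/5) = 0.943. This stands: the matter is one of power and reproducibility, not of validity. Relative efficiency does, however, leave out the lost degrees of freedom and the movement of the p-value between runs.

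It can also be said that planned power is roughly met. At the planned effect, the 2-df test with five imputations has power near .80 in several settings. This stands in part. In four of the six rows in step 6 it falls below 80% with five, and in all six it is above 80% with 50. The drop-out allowance compensates for data that are absent; the simulation noise comes on top and is avoidable.

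The loss could be smaller than computed. Table 1 lists many repeated measures that an imputation model could use, and good predictors would lower the FMI. That is fair, though at FMI 0.20 the shortfall is still 2.7 points. Twenty imputations would already recover most of the power, to about 79%; the case for 50 rests mainly on reproducibility.

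Finally, every finite number of imputations leaves some seed dependence, including 50, and stating a seed is a programming detail whose absence from an article is no fault. Both points are right. The number five, by contrast, is not left open: the article fixes it.

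**Conclusion.** The concern holds. The protocol fixes five imputations for a main analysis in which it expects 30% of participants to be lost. Compared with 50, this costs about 3 to 5 points of power for the 6-month contrast and about 4 to 6 for the overall test. It also leaves about a 7% to 15% chance that two runs on the same data disagree on significance when an effect of d = 0.5 to 0.64 is present.

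These figures rest on the assumptions listed in the working. Good auxiliary variables would reduce them, and a higher FMI would increase them. Validity is not threatened, so this is a worthwhile and nearly free improvement, not a serious flaw.

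**What to change.** In the Missing values section, replace five by at least 50 imputed data sets, a number well above the percentage of participants expected to be incomplete. It would help to fix and record the seed in advance, in the analysis plan or the program, so that the reported result can be reproduced. The Sample size calculation needs no change.

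The cost is one number in the text and a few minutes of computing. No participants, visits or data are added.
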